**Figure 3 figure3:**
[figure not shown]
Diagnostic assessment of the Cardiomyocyte injury following Acute Ischemic Stroke study. Illustration of the target points of the multimodal diagnostic workup to provide a thorough phenotyping of patients with stroke-associated myocardial injury. cMRI: cerebral magnetic resonance imaging; ECG: electrocardiogram; MRI: magnetic resonance imaging; TTE: transthoracic echocardiography.

Study endpoints.Primary outcome measuresFrequency of Takotsubo syndrome pattern on cardiovascular magnetic resonance imaging (CMR); consisting of wall motion abnormalities together with myocardial edema (T2 mapping) but without late gadolinium enhancementFrequency and extent of myocardial edemaFrequency of recent myocardial infarction on CMRFrequency and extent of ischemic and nonischemic myocardial fibrosis according to late gadolinium enhancement imaging and according to extracellular volume fraction on T1 mappingFrequency of left ventricular dysfunction in CMR (ie, ejection fraction and end diastolic left ventricular volume)Frequency of impaired left ventricular systolic and diastolic function in the transthoracic echocardiographySecondary outcome measuresFrequency of pathologic values of Periodic Repolarization Dynamics (PRDs) and Deceleration Capacity (DC; PRD≥5.75 deg²; DC≤2.5 ms)Frequency of values corresponding to *high perceived stress* in the Perceived Stress Scale (values ranging from 27 to 40)Frequency of cardiovascular events after 3 and 12 monthsFunctional outcome after 3 and 12 months assessed using the modified Rankin Scale.

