### Sample Size Calculation and Statistical Analysis

Regarding the primary hypothesis and based on the published literature, we expect a rate of acute myocardial edema on T2 mapping in CMR in approximately 15% of patients with acute myocardial injury [17,36]. In the comparison groups with no or chronic myocardial injury, we expect a significantly lower rate (approximately 2%) presenting with acute myocardial edema [37].

To show a significant difference between the groups (two-sided α=.05), a sample size of 48 patients per group is required to reach a power of 80% and 89 patients per group for a power of 90%. Taking into consideration that in previous studies, due to impaired compliance or technical problems, the complete protocol of CMR could be realized only in approximately 85% of the study patients, we aim to include approximately 100-105 patients in each group.

Group comparisons (when comparing between the 3 groups) of the primary and secondary outcome measures (frequencies of specific alterations in CMR, TTE, and ECG) will be conducted using the chi-square test for categorical variables and, in case of continuous variables, using one-way analysis of variance or Kruskal-Wallis test, as appropriate. When comparing 2 groups (group 3 vs group 1 or group 3 vs group 2), Student *t* test will be used to compare continuous data. Logistic regression analyses will be used to calculate odds ratios and 95% CI to examine the association between elevated hs-cTn levels and the presence of specific structural and functional cardiac alterations in CMR and TTE. Multiple regression analyses using backward selection will be used to identify factors associated with certain myocardial alterations or ECG findings.

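### Two-group contrasts of continuous data are tied to the Student t test, and PRD and DC are listed as outcomes only beyond fixed cutoffs; both rules can be improved with data already collected

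*Protocol article*

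**What the plan says.** In the Protocol article, Methods, Sample Size Calculation and Statistical Analysis, continuous outcomes across the three troponin groups are to be compared "using one-way analysis of variance or Kruskal-Wallis test, as appropriate". The next rule covers the pairs: "When comparing 2 groups (group 3 vs group 1 or group 3 vs group 2"), "Student *t* test will be used to compare continuous data". It has no qualifier and no rank-based option.

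Textbox 3 (study endpoints, Study Outcomes section) includes the extent of myocardial edema and of fibrosis among the primary outcomes, beside their frequencies. The expected edema rates are in the sample size section: "we expect a rate of acute myocardial edema on T2 mapping in CMR in approximately 15% of patients with acute myocardial injury", and for the other groups "we expect a significantly lower rate (approximately 2%) presenting with acute myocardial edema".

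The autonomic entry in Textbox 3 is a secondary outcome, the frequency of "pathologic values of Periodic Repolarization Dynamics (PRDs) and Deceleration Capacity", with cutoffs of PRD ≥5.75 deg² and DC ≤2.5 ms. The Abstract's Objective is to quantify autonomic dysfunction. The Discussion (Overview) says the two markers are so far unstudied in acute ischemic stroke.

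**The concern.** The two rules for continuous data do not match. A measure judged unsuitable for analysis of variance goes to Kruskal-Wallis across three groups and then to a Student t test for the pairs. Group 3 against 1 and group 3 against 2 are the contrasts that address the hypothesis about acute injury. If extent means lesion extent, the plan's own rates make edema extent zero in about 85% of one group and 98% of the other, so a comparison of means rests on very few patients.

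The PRD and DC entry raises a different issue. Cutting a continuous marker discards information, and the article offers no stroke-specific support for where the cuts fall. At stake is the chance of detecting a moderate autonomic difference, which is the study's second aim.

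**Working it through.** **The plan's own power figure.** There is one, for edema frequency (15% vs 2%, two-sided 0.05): 48 per group for 80% power and 89 for 90%. With n = [z₀.₉₇₅√(2p̄q̄) + z_power√(p₁q₁+p₂q₂)]²/(p₁−p₂)² and p̄ = 0.085:

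- 80%: (1.960×0.3944 + 0.8416×0.3835)²/0.0169 = 71.05, so 72 per group.
- 90%: (1.960×0.3944 + 1.2816×0.3835)²/0.0169 = 94.6, so 95 per group.

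At 48 and 89 per group this formula gives 63% and 88% power. The stated pair is therefore not reproduced. That is a separate matter, because the comparison is of proportions and uses no t test. The article gives no mean, SD, expected proportion or power for PRD, DC or any extent measure, so everything below rests on assumptions.

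**PRD and DC: continuous or cut.** Inputs: 100 per group (the planned size; the 85% completion figure concerns CMR, not the ECG), two-sided 0.05. Assumptions: normal values with equal SD, a shift of d SDs, and 10% to 50% of the comparison group beyond the cutoff.

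- Continuous: t test with noncentrality d√(n/2). For d = 0.4 this is 0.4×√50 = 2.83 on 198 df, giving 80.4%.
- Cut: power = Φ{[|p₁−p₂|√n − 1.96√(2p̄q̄)]/√(p₁q₁+p₂q₂)}. With 20% beyond the cut and d = 0.4, p₁ = 1−Φ(0.842−0.4) = 0.329, so power = Φ[(1.294−1.223)/0.617] = 54.6%.

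| Shift (SD) | Continuous | Cut: 10% / 20% / 30% / 40% / 50% beyond | Loss (points) |
|---|---|---|---|
| 0.2 | 29% | 14 / 17 / 19 / 20 / 20% | 9–16 |
| 0.3 | 56% | 26 / 34 / 38 / 39 / 39% | 17–30 |
| 0.4 | 80% | 43 / 55 / 60 / 61 / 61% | 19–37 |
| 0.5 | 94% | 62 / 75 / 79 / 80 / 79% | 14–32 |
| 0.6 | 99% | 79 / 89 / 92 / 92 / 91% | 7–20 |
| 0.8 | 100% | 97 / 99 / 99.5 / 99 / 99% | 0.5–3 |

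**Edema extent: t test or rank test.** Inputs: 85 per group (85% of 100 with complete CMR), edema in 15% vs 2%. Expected patients with any edema: 85×0.15 = 12.75 and 85×0.02 = 1.7. The size of non-zero values is assumed; power is by simulation with at least 3,000 datasets per row.

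| Non-zero extent | Severity in group 3 | Student t | Mann-Whitney |
|---|---|---|---|
| Log-normal, log-SD 1.0 | same | 64% | 91% |
| Log-normal, log-SD 0.8 | same | 74% | 91% |
| Log-normal, log-SD 0.8 | 1.5 times larger | 83% | 92% |
| Log-normal, log-SD 0.4 | same | 86% | 90% |
| Log-normal, log-SD 0.4 | 1.5 times larger | 95% | 92% |
| Uniform, 0.5 to 1.5 | 1.5 times larger | 96% | 92% |

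The t test thus ranges from about 27 points worse to about 4 points better. Its false-positive rate is not inflated: 4–5% with 15% non-zero in both groups, and 0.7–2.7% with 2% in both.

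**What the rank test measures here.** With so many ties, Mann-Whitney and the chi-square test of presence or absence reach the same decision in about 99% of datasets (91% power for each). The Hodges-Lehmann estimate is zero, because about 0.85×0.98 = 83% of between-group pairs differ by exactly zero, so the median difference is zero.

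**The case against.** Several stronger readings are tempting, and the article does not support them.

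- **That the plan loses a fixed 15 to 30 points of power.** No figure in the article implies this. The loss depends on assumed effects and distributions, and for edema extent the t test is sometimes the better test.
- **That the t test decides the primary question.** The powered comparison is a frequency. All six primary entries include or are frequencies, and only two add extent. PRD and DC are secondary.
- **That continuous analysis of PRD and DC is ruled out.** Study Outcomes refers to values of the ECG markers, and the statistical section provides tests for continuous outcomes and regression for ECG findings. The gap is that no continuous PRD or DC outcome is listed.
- **That Mann-Whitney would rescue edema extent.** It would mostly repeat the frequency test, which is already a primary outcome, whereas the t test asks about mean extent.
- **That all extent measures are mostly zero.** Extent is not defined, no late-enhancement rate is given, and extracellular volume fraction is a percentage that a t test may suit.

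It is also fair to say that this is a condensed article and that a fallback test is often left to an analysis plan. That would answer a silence. Here the article states a definite two-group rule that differs from its neighbour, and a definite autonomic outcome, so both remain open to comment.

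**Conclusion.** The point holds as two modest, separate improvements. For PRD and DC, the listed outcome gives up about 15 to 30 points of power under an assumed 0.3 to 0.5 SD shift at 100 per group. The loss is nearer 35 points when few patients lie beyond the cutoff and almost nil at 0.8 SD. The direction is the same throughout the grid, which assumes normal values with equal SDs.

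For two-group contrasts, the inconsistency with the three-group rule is certain from the text. Its effect on power is uncertain in size and even in sign for edema extent, so it supports allowing alternatives, not dropping the t test. Neither issue touches the edema-frequency comparison on which the sample size rests.

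**What to change.** 1. List PRD and DC as continuous secondary outcomes, on a log scale or with a rank-based test if skewed, and keep the frequencies beyond the cutoffs alongside.
2. For group 3 against 1 and group 3 against 2, replace the single test by Welch t for roughly normal measures, such as extracellular volume fraction, and Mann-Whitney for skewed ones, in line with the three-group rule.
3. Define extent. Where it is lesion extent and mostly zero, use a two-part analysis: presence by chi-square or Fisher test, then extent among those affected, with a bootstrap interval for the overall mean difference. Do not use Hodges-Lehmann, which would report zero.

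The second part will be largely descriptive for edema. About 13 and 2 affected patients are expected, and a comparison group of 85 would have none with probability 0.98⁸⁵ ≈ 18%. The bootstrap interval will be rough for the same reason.

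The cost is wording and a few extra analyses of secondary and extent measures. No new data are needed and the sample size does not change.

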## Introduction

### Background

Elevated cardiac troponin (cTn), which is a sign of myocardial injury, frequently occurs in the early phase after an acute ischemic stroke (AIS) and is associated with poor functional outcome, especially increased mortality [1,2]. Using high-sensitivity assays, cTn is detectable in more than 90% of stroke patients; 30%-60% have at least one cTn above the assay-specific 99th percentile upper reference limit (URL) [2,3]. Approximately 5%-20% show a rise/fall pattern indicating acute myocardial injury according to the fourth universal definition of myocardial infarction (MI) [4]. In the latter group, acute coronary syndrome has to be suspected [4-6]. Following the American guidelines (American Heart Association/American Stroke Association), it is specifically recommended to measure cTn in stroke patients [7,8]. However, recommendations on how to deal with elevated cTn in the context of AIS remain vague [8]. Furthermore, expert consensus documents on practical considerations on the clinical use of cTn list ischemic stroke as one of the illnesses that leads to clinical uncertainty in the context of interpretation of elevated cTn [9].

The phenomenon of acute brain injuries (including an ischemic stroke and intracranial hemorrhage) leading to cardiac complications, including elevated cardiac enzymes, is known for a long time. In reference to AIS, it has recently been described as stroke-heart syndrome (SHS) [10-13]. However, the exact pathophysiologic background of myocardial injury (ie, cTn elevation) after stroke is not entirely understood [13,14]. Several hypotheses have been discussed. Besides concomitant acute MI caused by atherothrombotic coronary artery disease (type 1 MI), situations of oxygen supply/demand mismatch have to be considered as underlying reasons. For example, tachyarrhythmia, hypotension/shock, anemia, or respiratory failure, which are frequently seen in stroke patients, can lead to a demand ischemia [4,15]. Furthermore, systemic conditions such as sepsis or chronic kidney disease may cause or facilitate myocardial injury [16].

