**Table 1 table1:** Definition of the 3 groups based on patients’ high-sensitivity cardiac troponin values.

Group	Description	hs-cTn^a^ values (URL^b^=14 ng/l)
Group 1	Normal hs-cTn levels	Both hs-cTn levels ≤URL
Group 2	Chronic myocardial injury (elevated but stable cTn levels)	At least one hs-cTn level >URL but *no* rise/fall (>20%) in serial measurements
Group 3	Acute myocardial injury (dynamic elevation)	At least one hs-cTn level >URL *and* rise/fall (>20%) in serial measurements^c^

^a^hs-cTn: high-sensitivity cardiac troponin.

^b^URL: upper reference limit (=14 ng/l).

^c^Or initial cTn value ≤URL and second value >URL+increase >50% URL (ie, 7 ng/l).

In addition to routine clinical procedures (refer to the *Baseline Visit* section), study patients receive a baseline assessment, an additional blood draw for biobanking, 3 Tesla (3T) cardiovascular magnetic resonance imaging (CMR), transthoracic echocardiography (TTE), and a 20-min high-resolution electrocardiogram (ECG) for a comprehensive assessment of cardiac autonomic function as well as a questionnaire testing cognitive function and the perception of stress. Furthermore, 3 and 12 months after discharge, patients will be followed up via structured telephone interviews for cardiovascular events and clinical outcomes (Figure 1).

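### The troponin exposure in the logistic regression, read literally, mixes chronic with acute injury, and the variable selection named separately is unsuited to rare CMR outcomes

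*Protocol article*

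**What the plan says.** All analysis statements come from the protocol article, Sample Size Calculation and Statistical Analysis.

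- **Premise.** For group 3, "we expect a rate of acute myocardial edema on T2 mapping in CMR in approximately 15% of patients with acute myocardial injury". For no or chronic injury, "we expect a significantly lower rate (approximately 2%) presenting with acute myocardial edema". Group 2 is therefore a comparison group.
- **Group tests.** Chi-square, analysis of variance or Kruskal-Wallis across the three groups. Two-group comparisons are group 3 against 1 or group 3 against 2.
- **Logistic regression.** Odds ratios are computed "to examine the association between elevated hs-cTn levels and the presence of specific structural and functional cardiac alterations in CMR and TTE". How the exposure is coded is not given.
- **Variable selection.** A separate sentence reads: "Multiple regression analyses using backward selection will be used to identify factors associated with certain myocardial alterations or ECG findings". It names neither candidate factors nor specific outcomes.

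Table 1 (Study Design) describes group 2 as "Chronic myocardial injury (elevated but stable cTn levels") and group 3 as dynamic elevation. Both therefore count as elevated. Background notes that "systemic conditions such as sepsis or chronic kidney disease may cause or facilitate myocardial injury", while the exclusion criteria remove only patients with an eGFR below 30.

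**The concern.** The study's hypothesis concerns acute injury. The Discussion expects more edema and more functional change in patients with acute, dynamic troponin elevation. An exposure that also takes in stable elevation answers a different question. For edema it adds to the exposed side a group that the plan itself assumes to behave like the unexposed. The resulting odds ratio would not be the one for acute injury.

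Backward selection is the only method the article explicitly describes as multivariable. It keeps or drops variables on p-values, so it can remove a confounder that matters, and intervals computed as if the final model had been fixed in advance are too narrow. Both problems weigh most when events are few. The main CMR outcomes are expected to be rare: the Takotsubo pattern (first-listed primary outcome) requires edema without late enhancement, and recent infarction requires edema with it. Both are subsets of edema.

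**Working it through.** **Inputs from the article.** "two-sided α=.05"; edema in 15% of group 3 and in 2% of each of groups 1 and 2; 100 to 105 patients per group with about 85% completing CMR, so about 85 to 89 evaluable per group. The Abstract and Results instead plan 300 patients with complete CMR, which is 100 per group. Both 85 and 100 are carried through.

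**The plan's own figures.** The article states 48 per group for 80% power and 89 for 90%. With the two-sided pooled-variance formula for 15% vs 2%:
- 1:1 needs 72 for 80% and 95 for 90%. Power is 63% at 48 per group and 88% at 89.
- 48 is matched at 2:1, that is, 48 in group 3 against 96 in groups 1 and 2 together (80.3%). For 90%, 2:1 gives 67.

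No single formula tried gives both figures. That is a separate matter and does not affect what follows.

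**Odds ratios implied by the planning rates.**
- Group 3 vs 1: (0.15/0.85)/(0.02/0.98) = 8.65.
- Groups 2 and 3 combined, equal sizes: rate (0.15 + 0.02)/2 = 0.085. Against group 1: (0.085/0.915)/(0.02/0.98) = 4.55.

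**Power**, using the two-proportion z test in place of the test of the odds ratio. Power = Φ[(difference − 1.96 × SE0)/SE1], with SE0 from the pooled rate and SE1 from the separate rates.
- 85 vs 85: SE0 = √(2 × 0.085 × 0.915/85) = 0.0428; SE1 = √[(0.15 × 0.85 + 0.02 × 0.98)/85] = 0.0416; (0.13 − 0.0839)/0.0416 = 1.11; power 87%.
- 170 vs 85: pooled rate (14.45 + 1.7)/255 = 0.0633; SE0 = 0.0324; SE1 = 0.0262; (0.065 − 0.0634)/0.0262 = 0.06; power 52%.
- 100 per group, same formula: 92% for group 3 vs 1, and 61% for 200 vs 100.

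**Precision** (Wald 95% intervals at the expected counts).

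| Contrast for edema | OR | 85 per group | 100 per group |
|---|---|---|---|
| Group 3 vs 1 | 8.65 | 1.7 to 44 | 1.9 to 39 |
| Groups 2+3 vs 1 | 4.55 | 0.91 to 22.8 | 1.03 to 20.1 |

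**Expected edema events.** n × (0.15 + 0.02 + 0.02): 85 × 0.19 = 16.2; 100 × 0.19 = 19.0. The Takotsubo pattern and recent infarction exclude each other, so together they share at most this number.

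**Chance of an empty cell for edema.**
- Group 1: 0.98^85 = 18%; 0.98^100 = 13%.
- At least one of groups 1 and 2: 1 − (1 − 0.180)² = 33%; 1 − (1 − 0.133)² = 25%.

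With no event in a group, ordinary logistic regression has no finite odds ratio for contrasts with that group.

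**The case against.** **A reader might infer that the plan pools groups 2 and 3.** It does not say so. A three-level factor, separate contrasts or the troponin level itself all fit the wording, and the same section keeps group 3 vs 1 and group 3 vs 2 apart for two-group tests. The article states no planned odds ratio, and its sample size is not tied to this regression. This stands: the defect is an exposure left ambiguous, whose literal reading conflicts with the planning premise. It also stands that the dilution is shown for edema only. The article treats fibrosis as a correlate of chronic injury, so counting group 2 as exposed need not weaken fibrosis odds ratios.

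**A reader might infer that backward selection produces the troponin odds ratios or is applied to edema.** The two analyses are in separate sentences, and the selection may concern ECG markers or continuous CMR measures in 255 to 300 patients. This stands, so the event-count argument is conditional. The wording does admit edema, which is central to the stated outcomes.

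**A reader might cite how often selection retains pure-noise factors as proof of few-event instability.** That does not follow. Testing k independent noise factors at 5% gives 1 − 0.95^k, which is 34%, 46% and 54% for k = 8, 12 and 15, whatever the number of events. Simulated backward selection gave 31%, 46% and 51%, which is ordinary multiplicity.

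**A reader might conclude that the analyses are unadjusted or badly adjusted.** A condensed article commonly leaves the covariate list to a fuller document, so no such claim is made. Nor do the documents give the figures needed to size any confounding. The article itself says that its autonomic measures can show only association.

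**The remedy is itself demanding.** A three-level factor (two parameters) plus age, sex and eGFR makes five parameters on 16 to 19 events, or 3.2 to 3.8 per parameter. Firth estimation keeps estimates finite and reduces bias but adds no information, so intervals will stay wide. A model of group 3 against groups 1 and 2 together would have less empty-cell risk (0.98^170 = 3%) but would not separate acute from chronic injury.

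**Conclusion.** The point holds in a limited form, as an inexpensive improvement rather than a flaw that invalidates the plan. The exposure wording permits a model at odds with the plan's own premise. If coded that way, the edema odds ratio falls from 8.65 to 4.55 and power from 87% to 52% (85 evaluable per group) or from 92% to 61% (100 per group). These figures rest on the planning rates of 15%, 2% and 2%, equal group sizes and the literal reading of the exposure.

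Backward selection is a poor choice for any rare binary CMR outcome. For edema it would have about 16 to 19 events, and fewer for each of its subsets. Whether it will be used there is not stated. The empty-cell risk of 13 to 18% in group 1, and 25 to 33% in at least one of groups 1 and 2, follows from the planning rates alone.

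**What to change.** 1. Replace the exposure wording with troponin group as a three-level factor, reporting odds ratios for group 3 vs 1 and group 3 vs 2.
2. For these associations, fix a small covariate set in advance: age, sex and eGFR. Adjustment for prior cardiac disease is optional and debatable, because it overlaps with the fibrosis and dysfunction outcomes.
3. For rare binary CMR outcomes (edema, Takotsubo pattern, recent infarction), use Firth penalised logistic regression with profile-likelihood intervals.
4. Keep backward selection only as an analysis labelled exploratory, separate from the troponin-group odds ratios.

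The cost is analysis wording. Age and sex are baseline demographics, and eGFR is needed for eligibility, so no new data are required. The downside is that the data-driven search for associated factors becomes exploratory. Adjusted intervals for the rare outcomes will remain wide.
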